## Abstract

**Background:**

Laparoscopic cystectomy is currently considered the gold standard for the treatment of ovarian endometrioma, resulting in an improvement in symptoms, a lower recurrence rate, and a higher pregnancy rate among infertile patients. However, this treatment is not free from risk, since it is associated with a reduction in ovarian reserve. There is still controversy in the literature regarding whether the cause of the reduction in ovarian reserve is due to damage caused by the coagulation energy during hemostasis or whether the procedure itself is the cause of the damage irrespective of the hemostatic method used. The aim of this study is to compare the effects of different hemostatic methods on the ovarian function of women subjected to laparoscopic surgery for ovarian endometrioma.

**Methods:**

An open-label randomized clinical trial to be conducted at the Lauro Wanderley University Hospital between December 2017 and August 2020. Eighty-four patients will be randomly allocated to three groups according to the hemostatic technique used during laparoscopic surgery for ovarian endometrioma: bipolar coagulation; laparoscopic suture; and hemostatic matrix. Ovarian function will be assessed by serum anti-Müllerian hormone measurement and by performing an antral follicle count using ultrasound before surgery and one, three, and six months after surgery. The internal review board of the Medical Sciences Center, Federal University of Paraíba approved the study protocol under reference CAAE 71621717.9.0000.8069.

**Discussion:**

Bearing in mind the need for more randomized clinical trials to clarify this issue, we hope to contribute with data that will determine whether there is any difference between hemostatic methods despite the rational use of bipolar energy or whether the procedure itself explains the ovarian damage irrespective of the hemostatic technique used.

**Trial registration:**

ClinicalTrials.gov, NTC03430609. Registered on XX.10/31/2017.

ISRCTN Registry, ISRCTN11469394. Registered on XX.17/12/2017.

Unique Protocol ID: U1111–1203-2508.

## Background

Ovarian endometriomas are present in 17–44% of women with pelvic pain and infertility. There is considerable controversy regarding aspects that range from variations in the physiopathology of endometriomas to the different forms of treatment [1, 2]. Treatment may consist of conservative management or surgery. Surgical procedures include aspiration of the chocolate-colored fluid from the endometrioma, drainage of the cyst followed by bipolar coagulation, fenestration and laser ablation, cystectomy with complete resection of the endometrioma wall, or even oophorectomy in exceptional cases [3–5].

Laparoscopic cystectomy appears to be the ideal treatment option when surgery is required. This procedure offers favorable results in terms of improving pelvic pain and reducing recurrence rates of the endometrioma [4, 6, 7]. Nevertheless, the technique is not without risk and may result in damage to ovarian function, either from the inadvertent removal of healthy ovarian parenchyma or as a consequence of the thermal effect of coagulation on bleeding points [8–13].

Findings that the surgical treatment of endometriomas can damage ovarian function led to several studies being conducted, resulting in hundreds of publications on the subject. However, no definitive answers have been found. Whereas some studies reached the conclusion that surgery is responsible for ovarian damage [4, 7, 11, 14–26], others reported that the mere fact that the patient had an endometrioma justifies the damage, since the disease in itself constitutes a major cause [27–35].

In relation to the surgical technique used, the majority of investigators agree that the use of bipolar coagulation is responsible for a decrease in ovarian function when this technique is compared with hemostasis with suture or with the use of hemostatic agents [9–13]. Nevertheless, the available evidence is inconclusive, since some studies have failed to find any significant decrease in ovarian function [6, 36–39].

Ata et al. recently conducted a meta-analysis that included six studies, four of which consisted of randomized clinical trials (RCT). Of these, two included only patients with bilateral endometriomas, a situation that is known to be associated with an increased risk of impaired ovarian function compared to unilateral endometriomas, irrespective of the hemostatic technique. Furthermore, the investigators concluded that the quality of the evidence in the studies analyzed in that meta-analysis was moderate and that it would be advisable to avoid the use of bipolar energy whenever possible. In view of the small magnitude of the effect, the possible side effects and the additional cost of hemostatic agents, it is not possible to recommend substituting bipolar coagulation with another method. Indeed, those investigators suggested that further RCTs should be conducted to compare different hemostatic techniques [13].

Another meta-analysis included some widely heterogenous studies that compared laparoscopy with laparotomy, used different methods for the evaluation of ovarian function, and included cases of bilateral endometriomas. The authors suggested that new clinical trials should be conducted to compare different hemostatic methods in order to provide further clarification [12].

Notably, none of the studies in which bipolar coagulation was evaluated provided details on how the bipolar energy was used, stating only the voltage that was applied. Therefore, there are no precise data on how many points were coagulated or for how long cauterization was performed.

There are also controversies in relation to the methods used to evaluate ovarian function. The most commonly used methods are measuring anti-Müllerian hormone (AMH) and follicle-stimulating hormone (FSH) levels and performing antral follicle count (AFC) by ultrasound. Some studies have found AMH to be the most accurate, since this method provides a systemic evaluation with little variation during the menstrual cycle. Other studies have indicated AFC as the best method, since evaluation is performed specifically on the affected ovary, without the effect of any possible compensation by the contralateral ovary. Furthermore, some studies have shown a reduction or no change in AMH, while others have shown no change or even an improvement in AFC following the treatment of endometriomas [40–44].

Another point that has to be taken into consideration is that when endometriomas are compared to cysts of other types, AMH levels seem to be lower in the case of endometriomas even before surgery [27–35]. After surgery, there appears to be a similar decrease, irrespective of the etiology of the cyst [45–47]; however, this decrease is temporary, with a tendency to recover over subsequent months [39, 48–52].

In view of these considerations, the objective of the present study is to evaluate the effect on ovarian function of three different methods of hemostasis (bipolar coagulation versus suture versus hemostatic agents) in patients submitted to oophoroplasty because of an endometrioma, with ovarian function being assessed by measuring AMH and by performing AFC. The use of bipolar energy will be described in detail, including the number of points coagulated during the procedure. To the best of our knowledge, no other study has been conducted to evaluate the three different methods in the same clinical trial.

## Methods

Figure 1 provides an overview of the methodology of the trial. The flow chart will be completed according to the Consolidated Standards of Reporting Trials (CONSORT) 2010 guidelines [53].

**Fig. 1 Fig1:**
[figure not shown]
*Flow chart* of the trial

### Study design

An open-label RCT will be performed to compare the impact of hemostatic techniques (bipolar coagulation versus laparoscopic suture versus hemostatic matrix) during laparoscopic surgery for an ovarian endometrioma on the ovarian follicular reserve.

### Study population and setting

Patients with ovarian cysts suggestive of endometriomas, diagnosed by ultrasonography, who are receiving care at the gynecological endoscopy outpatient clinic of the Lauro Wanderley University Hospital (HULW) during the study period, will be screened for inclusion in the study.

### Eligibility criteria

Women aged at least 18 years, with regular menstrual cycles (21–35 days) and a diagnosis of a unilateral ovarian cyst suggestive of an endometrioma, with an indication for laparoscopic surgery to remove the cyst due to pelvic pain, infertility, or persistence of the cyst will be eligible for the study. Exclusion criteria are: previous ovarian surgery; endocrine dysfunction (diabetes, thyroid disorders, hyperprolactinemia, adrenal disease, polycystic ovary syndrome); use of hormones in the past three months; suspected malignant ovarian tumor requiring oophorectomy; history of chemotherapy or radiotherapy; coagulation disorders; pregnancy; and autoimmune disease.

### Participant selection and randomization

Eligible patients will be invited to participate in the study and those who accept the invitation will be admitted.

The sample will be divided into three groups according to the hemostatic technique used:Bipolar coagulation (bipolar Maryland, ref.702505ML, Astus Medical©, Copyright 2015, Tampa, FL, USA) with 30-W power and a Valleylab generator (Medronic©, Copyright 2017, Medtronic Parkway, Minneapolis, MN, USA). The number of coagulated points will be counted; the time for coagulation will be measured in seconds.Laparoscopic suturing with simple suture (2–0/Vicrylpolyglactin absorbable synthetic suture; Ethicon Inc., NJ, USA). The number of sutures will be recorded.Hemostatic matrix (Surgicel® Original Absorbable Hemostat, Ethicon, USA).

Randomization to receive the various hemostatic techniques (bipolar coagulation, laparoscopic suture, or hemostatic matrix) during laparoscopic surgery for endometrioma will be performed based on a list of sequential numbers generated using the Random Allocation software package, version 2.0. The list will consist of numbers in the range of 1–84 (the total number of participants to be randomized) and the letters A, B, and C, which will designate the study groups. An individual not directly involved in the study will prepare opaque envelopes numbered 1–84, which will contain the group to which the patient must be allocated.

At the time of inclusion, a number will be assigned to each participant, corresponding to her order of entry in the study. During surgery, at the time of hemostasis, a nurse at the surgical theater will open the envelope containing the corresponding number. Thus, allocation will remain concealed up to that specific moment during surgery, since it is impossible to blind the surgeon to the technique to be used.

### Sample size

Sample size was calculated using resources available at the Laboratory of Epidemiology and Statistics (LEE) website of the Dante Pazzanese Institute (http://www.lee.dante.br/pesquisa/amostragem/qua_2_medias.html). The calculation was based on data provided by Sönmezer et al. [48]. In that article, Sönmezer et al. detected a significant difference in the serum levels of AMH in the first month after surgery, with a measurement of 2.72 ± 1.49 for the patients who received the hemostatic matrix versus 1.64 ± 0.93 for the patients who received bipolar coagulation. Here, we assume that the standard deviation in the AMH measurement of 1.49 in the first month was significant, since that was the number that generated the largest sample size when compared with other values from that article. The difference to be detected is 1.08, which corresponds to the mean difference in AMH in the first month between the patients who receive hemostatic matrix and those who receive bipolar coagulation. On those grounds, and for a statistical power of 80% (*p* = 0.05), each group would have to have 23 participants. Considering possible losses, the sample will be increased by 20% to 28 participants per group, making a total of 84 women. It should be noted that the present sample maybe not detect a powerful difference in treatment arms, but relevant contributions are expected.

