#### Data processing and analysis

The data will be double-entered by two different data entry operators, using the Epi Info software program, version 7.2. The two databases will be compared using the Validate function of the Epi Info software program. Statistical analysis will be conducted using the Microsoft Excel software and the SPSS statistical software package for Windows, version 19.0.0. The data entry operators and the statistician will be blinded in that they will receive the data marked simply as A, B, or C and will be unaware of which procedure corresponds to which letter. A significance level of 5% will be determined for all the statistical tests.

To analyze the numerical variables AMH and AFC, the Kolmogorov–Smirnov test of normality will be used to determine the type of analysis to be performed. If distribution is normal, two-way analysis of variance (ANOVA) will be used, with the group representing an independent factor (bipolar energy × suture × hemostatic matrix). Another factor to be analyzed will be paired time points (before surgery × 1 month × 3 months × 6 months). If distribution is not normal, non-parametric tests will be used to analyze the variables.

The Kruskal–Wallis test will be used to compare variables between the three groups at each time point, with Tukey’s multiple comparison test being used when comparisons are statistically significant. The Friedman test will be used to perform intra-group comparisons at the four evaluation moments, with Tukey’s multiple comparison test being used when they are significant.

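### On the stated inputs, 23 women per group do not give 80% power for a two-sided 5% comparison of matrix with bipolar; power is about 67% with 23 evaluable and 76% with 28

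*Protocol article*

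**What the plan says.** The Sample size section of the protocol article bases the calculation on one-month AMH in an earlier study: 2.72 ± 1.49 with hemostatic matrix and 1.64 ± 0.93 with bipolar coagulation. It uses an online calculator for two means.

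- Difference: "The difference to be detected is 1.08", which is 2.72 − 1.64.
- SD: "we assume that the standard deviation in the AMH measurement of 1.49 in the first month was significant". The reason given is that this value produced the largest sample.
- Power and level: "for a statistical power of 80" per cent, with p = 0.05. Sidedness is not stated.
- Result: "each group would have to have 23 participants".
- Losses: "Considering possible losses, the sample will be increased by 20% to 28 participants per group, making a total of 84 women".

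The section ends with a loosely worded warning that the sample may not be large enough to show a difference between arms.

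The Data processing and analysis section sets the level: "A significance level of 5% will be determined for all the statistical tests". If AMH and AFC are normally distributed, it plans a two-way ANOVA on group and time. Otherwise it goes to rank tests: "The Kruskal–Wallis test will be used to compare variables between the three groups at each time point". Pairwise follow-up by Tukey's method is conditional on that overall result; the article describes it as a "multiple comparison test being used when comparisons are statistically significant".

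**The concern.** The section prints every input except sidedness, so its result can be checked. The result does not follow from the inputs under the two-sided test that matches the planned analyses. ANOVA and Kruskal–Wallis have no direction, and no one-sided hypothesis appears in the article. The calculation also covers one contrast between two arms, whereas the analysis compares three.

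The stake is how a null result will be read. The Discussion says that if no significant differences appear, surgeons may choose whichever method is most convenient. A reader who believes the 80% figure takes the chance of missing a true difference of 1.08 to be 20%. If that chance is nearer one in three, a non-significant comparison says much less.

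**Working it through.** **Inputs (Sample size section):** difference Δ = 1.08; common SD σ = 1.49; α = 0.05; power 0.80. Standardised difference: 1.08 / 1.49 = 0.725. Ratio: σ²/Δ² = 2.2201 / 1.1664 = 1.903.

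**Formula:** n per group = 2(z_α + z_power)² × σ²/Δ², with z_power = 0.842.

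**1. Looking for the plan's 23**
- One-sided 5%: 2 × (1.645 + 0.842)² × 1.903 = 23.5, strictly 24 when rounded up. The t test gives 24.2, so 25.
- So 23 is near the one-sided result but falls slightly short of it. One-sided t-test power at 23 is 78%.

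**2. Two-sided 5%, matching the non-directional analyses**
- 2 × (1.960 + 0.842)² × 1.903 = 29.9, so 30. The t test gives 30.9, so 31.

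**3. Power at the planned sizes (two-sided 5%)**

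| Evaluable per group | Normal formula | t test |
|---|---|---|
| 23 | 69% | 67% |
| 28 | 77% | 76% |
| 31 | – | 80% |

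On the t test, the chance of missing a true difference of 1.08 is 33% at 23 per group and 24% at 28, against the implied 20%.

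**4. Three arms (illustration only)**
For the same difference and SD, a normal-theory Tukey comparison among three groups has power of 53% at 23 per group and 63% at 28. It reaches 80% at about 40 per group. The article does not specify exactly this procedure: it names Tukey only after a significant Kruskal–Wallis or Friedman test. The figures show the direction and rough size of the loss. They are not the power of the written analysis.

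**5. Another SD**
Using both source SDs, √((1.49² + 0.93²)/2) = 1.24. The two-sided formula then gives 20.8, so 21 (22 by the t test), and t-test power at 23 is 82%. This does not explain the printed figure, because the section says it used 1.49.

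**6. Loss allowance**
23 × 1.2 = 27.6, so 28. This agrees with the text.

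**7. Baseline adjustment (assumed correlation ρ between baseline and one-month AMH)**
The residual SD is 1.49 × √(1 − ρ²). With 23 per group, two-sided 5%, t-test approximation:

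| ρ (assumed) | Residual SD | Power |
|---|---|---|
| 0.3 | 1.42 | 71% |
| 0.5 | 1.29 | 79% |
| 0.7 | 1.06 | 92% |

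The article gives no value for ρ.

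**The case against.** **The SD is conservative.** With both source SDs, 23 per group has 82% power, so the real shortfall may be smaller or absent. This stands as context. It does not rescue the statement, because the article claims the cautious SD and then prints a sample size which that SD does not support.

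**The article admits the limit.** Its closing sentence does warn the reader. But it gives no figure and does not withdraw the 80%.

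**A reader might infer that the authors ran a one-sided test.** The arithmetic points that way, but the documents do not establish it. Sidedness is unstated, the calculator's settings are not shown, and the one-sided result rounds up to 24 or 25. What can be said is that 23 is not reproduced two-sided.

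**A reader might infer that the trial's power is 53% to 63%.** The documents do not support that as a description of the plan. The ANOVA branch names no Tukey test, and in the rank-test branch Tukey follows only a significant overall test.

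**A reader might infer that the allowance for losses is also wrong**, since 23 / 0.8 = 28.75 would need 29. The text says the sample is increased by 20%, and it is. It never states an expected dropout of 20%. Twenty-eight women still leave 23 after five losses (5/28 = 17.9%). This is not an error.

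**Conclusion.** The stated 80% power is wrong as written. For a difference of 1.08, SD 1.49 and a two-sided 5% comparison of two groups, 30 to 31 evaluable women per group are needed. The planned numbers give about 67% (23 evaluable) to 76% (28 evaluable), so even with no losses the claim is not met.

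This rests on the article's own difference and SD, a t test on one-month AMH, and a two-sided test. The last is inferred from the non-directional analyses, because sidedness is not declared. The suture comparisons have no target difference in the article, so no power can be stated for them. Any multiplicity-adjusted pairwise comparison has lower power than the unadjusted one for the same difference.

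**What to change.** Keep 84 women and rewrite the Sample size paragraph to:

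1. State that the test is two-sided at 5%.
2. Replace the 80% claim with about 67% power (23 evaluable per arm) to 76% (28 evaluable) for the unadjusted matrix versus bipolar contrast on one-month AMH, at difference 1.08 and SD 1.49.
3. State that the suture comparisons and the adjusted pairwise comparisons were not sized, and that adjustment lowers power for a given difference.
4. Amend the Discussion so that a non-significant result is not taken to show that the methods are interchangeable.

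Adjusting for baseline AMH, which Table 1 already schedules, would be a useful addition and needs no new data. Any power quoted for it should be labelled as resting on an assumed correlation, and should not replace the figures in item 2.

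The cost is a few sentences and a less favourable power statement, with no extra patients. The Trial status section reports 32 women randomized at 24 April 2019, so at that date the correction could still be made before the final analysis.

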### Procedures for the assessment of ovarian reserve

Ovarian reserve will be assessed by measuring AMH and by performing AFC using ultrasonography at four different moments: before surgery and one, three, and six months after surgery. Serum samples will be obtained from each participant and centrifuged for 10 min to separate the cell contents and debris. Each serum sample will be transferred to polypropylene tubes and stored at − 80 °C.

AMH levels will be quantitatively measured using enzyme-linked immunosorbent assay (ELISA) (Diagnostic Systems Laboratories, Webster, TX, USA), with a detection sensitivity of 0.006 ng/mL.

Transvaginal ultrasonography for antral follicle count will be performed during the early proliferative stage (days 3–7 of the menstrual cycle) and the total number of follicles with diameters < 10 mm will be considered.

### Procedures for laparoscopic surgery

The same surgeon will perform all the surgical procedures, with the participants under general anesthesia and in a semi-lithotomy position. A 10-mm umbilical puncture will be performed for the camera after insufflation of the pneumoperitoneum. Three additional 5-mm punctures will be performed on the right iliac fossa, left iliac fossa, and suprapubic area to allow the instruments to be inserted. Intra-abdominal pressure will be maintained at approximately 15 mmHg.

Endometriosis will be classified according to the 1997 Revised American Society for Reproductive Medicine (ASRM) classification. In all the groups, endometriomas will be removed using traction-countertraction techniques. Adhesiolysis will be performed to separate the ovary from the adjacent structures, as necessary. In case of cyst rupture, the contents will be aspirated and the site of spillage will be thoroughly rinsed.

In the group allocated to receive bipolar coagulation, hemostasis will be performed using bipolar tweezers at 30 W as few times as possible, just to control any considerable bleeding. The number of coagulated points will be recorded and the duration of the procedure at each bleeding point will be measured. These parameters will help clarify any possible flaws in previous studies that failed to specify the number of coagulated points or the duration of coagulation at each point.

In the group allocated to receive hemostasis by laparoscopic suture, the procedure will involve simple intra-ovarian sutures (1 or 2 knots with 2–0 Vicryl) and the number of sutures will be counted.

In the group allocated to receive hemostasis by hemostatic matrix, the sealant will be applied on the ovarian wound surface.

